### Statistical analyses

The efficacy analysis will be performed by intention-to-treat analysis, including all patients from whom a follow-up assessment is available. If necessary a multiple imputation technique will be used for missing data. The primary outcome will be analysed by using Generalized Estimated Equations (GEE) for repeated measures, with baseline BMI as covariate and time, intervention and the interaction of time and intervention as fixed variables. The secondary outcomes will be analysed with ANCOVA on the change from baseline to follow-up. In addition differences in characteristics (e.g. age, sex, education level) of participants and non-participants will be evaluated.

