### Measurements

#### Clinical measures

In both groups, BMI, systolic blood pressure, HbA1c and lipid profiles will collected from the electronic medical record at baseline and 2.5 years follow-up. Clinical measures in-between will also be extracted from the electronic medical record of the GP.

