### Sample size

In our previous study, the self-management intervention BGI achieved a significant BMI reduction of 0.77 after 9 months in screen-detected T2DM patients (BMI −0.39 in the intervention group vs. +0.38 in the control group) [2]. For the current study a minimum sample size of 88 (44 per group) is required to achieve 80% power to detect a difference of 0.77 in a design with 6 repeated measurements of BMI (weight is measured every three months as part of usual diabetes care) having a AR (1) covariance structure when the standard deviation is 1.7, the correlation between subsequent observations on the same subject is 0.70, and alpha 0.05. With an expected drop-out rate of 20%, we need to include a total of 106 patients.

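### The analysis called intention-to-treat keeps only patients with a follow-up assessment and leaves imputation optional, so the BMI effect can be biased if drop-out depends on earlier BMI and differs by arm

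*Protocol article*

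**What the plan says.** All references are to the protocol article.

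- **Statistical analyses, analysis set:** the efficacy analysis is an "intention-to-treat analysis, including all patients from whom a follow-up assessment is available".
- **Statistical analyses, missing data:** "If necessary a multiple imputation technique will be used for missing data". The article gives no condition for this.
- **Statistical analyses, models:** BMI is analysed by "Generalized Estimated Equations (GEE) for repeated measures, with baseline BMI as covariate and time, intervention and the interaction of time and intervention as fixed variables". No working correlation is named. Secondary outcomes are analysed by ANCOVA on change from baseline to follow-up.
- **Primary outcome measure:** follow-up is placed 2.5 years after the start of the programme.
- **Clinical measures:** BMI, blood pressure, HbA1c and lipids come from the electronic record at baseline and 2.5 years, and "Clinical measures in-between will also be extracted from the electronic medical record of the GP".
- **Sample size:** "a minimum sample size of 88 (44 per group) is required to achieve 80% power to detect a difference of 0.77", with six repeated BMI measurements "having a AR (1) covariance structure when the standard deviation is 1.7" and a correlation of 0.70. Then: "With an expected drop-out rate of 20%, we need to include a total of 106 patients".

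**The concern.** An intention-to-treat set contains everyone randomised, in the arm to which they were assigned. Requiring a follow-up assessment selects on a post-randomisation event, so the label and the rule disagree. Imputation does not clearly repair this: it is conditional, and patients without a follow-up assessment are already outside the set to which it would apply.

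The meaning of a follow-up assessment also matters. If any later BMI value counts, few patients are lost. If it means the 2.5-year assessment, which is how the outcome section uses the word, the set is completers only and the earlier values of patients who leave are thrown away. Those values carry the information needed to correct for drop-out that depends on earlier BMI.

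The expected loss is not negligible: 20% of 106 is about 21 patients. Allocation is open and only one arm attends a course, so drop-out that differs by arm is possible. At stake is the primary BMI estimate, and through the ANCOVA the clinical secondary outcomes.

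**Working it through.** **1. Reproducing the plan's figure, to confirm the inputs.** From Sample size: SD 1.7, six measurements, AR(1) with correlation 0.70, difference 0.77, power 80%, alpha 0.05 (taken as two-sided).

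Variance factor for the mean of six values: (1/36) × Σ 0.7^|i−j| = 0.563. Effective SD = 1.7 × √0.563 = 1.276.

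n per group = 2 × (1.96 + 0.84)² × 1.276² / 0.77² ≈ 43.1, rounded up to 44. The stated 44 per group is reproduced (power 80.8% at 44), so these inputs describe the data the plan has in mind.

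**2. Large-sample simulation with those inputs.** True difference -0.77 at every visit; simulation error about 0.01. The drop-out mechanisms are assumptions, because the article gives none.

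*Set A: 200,000 patients per arm, 20% lost in each arm by the last visit.* In the BGI arm drop-out depends on the last observed BMI value; in control it is random. Difference at the last visit:

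| Analysis | Log-odds slope 0.5 per SD | Slope 1.0 per SD |
|---|---|---|
| GEE, independence, no imputation | -0.85 | -0.90 |
| Completers only, AR(1) weighting | -0.85 | -0.89 |
| GEE, AR(1), all available values | -0.78 | -0.76 to -0.77 |
| GEE, exchangeable, all available values | -0.75 | -0.73 |

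Overstatement in the first row: (0.85 − 0.77)/0.77 = 10% and (0.90 − 0.77)/0.77 = 17%. When both arms share the mechanism, each relative to its own mean, independence GEE gives about -0.77: no bias.

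*Set B: 200,000 patients in total, 16–20% lost by the last visit.*

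| Drop-out depends on | GEE, independence | GEE, AR(1) | Multiple imputation by arm |
|---|---|---|---|
| Nothing (completely random) | -0.76 | -0.76 | -0.76 |
| Baseline BMI only | -0.76 | -0.76 | -0.76 |
| Previous BMI, same direction in both arms, common reference value | -0.72 | -0.76 | -0.77 |
| Previous BMI, opposite directions | -0.98 | -0.77 | -0.77 |

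In the third row the common reference value makes control lose more patients (23.5% against 16.6%), so the arms still differ in drop-out and the bias runs against BGI.

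**3. Reading the results.** Drop-out that is random or driven by a modelled covariate does no harm. Drop-out that depends on earlier BMI and differs by arm biases the independence GEE in either direction. Set A shows that AR(1) weighting rescues the estimate only while the partial follow-up is kept: on completers the bias returns in full.

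**The case against.** A reader might infer that the plan's estimate is unbiased only if drop-out is completely random, that any bias must favour BGI, and that GEE has to be replaced. The article supports none of these.

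- GEE tolerates drop-out that depends on modelled covariates. With a correct AR(1) working correlation on all available values, it matched the truth even when drop-out depended on earlier BMI. AR(1) is the structure that the Sample size section names, although the analysis section does not carry it over. Proper imputation also needs only missing at random.
- The direction follows from the mechanism chosen: the runs gave -0.72, no bias, and -0.98.
- BMI comes from the GP record in both arms, weight is measured every three months in usual care, and usual care is the same in both arms. Leaving the course does not in itself remove BMI values, so fewer than 20% may be lost.
- A shift of 0.08 to 0.13 is small beside a last-visit standard error of about 1.7 × √(2/44) = 0.36.
- If one later value suffices for inclusion, the set is nearly what a mixed model would use anyway, since patients with no post-baseline BMI add nothing to it.
- ANCOVA on change is standard, and the imputation sentence is not limited to BMI. The imputation model, its trigger and the working correlation may stand in a fuller document.

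All of this stands, and it limits the claim. It does not remove the stated rule, which selects on a post-randomisation event under an intention-to-treat label and can be read as completers only. A later document that filled in the imputation details would still have to change that rule.

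**Conclusion.** The concern holds in limited form. The analysis set contradicts its label, may exclude patients whose in-between values are already being extracted, and leaves the only stated remedy optional. If imputation is not used, the primary result is valid for drop-out that is random or depends only on arm, time and baseline BMI. If drop-out depends on earlier BMI and differs by arm, a completers-only set or an independence GEE is biased: -0.85 to -0.90 instead of -0.77 when 20% are lost and only BGI drop-out is informative. That example rests on the plan's SD and correlation and on an assumed mechanism. The real size and sign cannot be derived from the article. The rule is worth changing before analysis because it decides who counts in the primary comparison.

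**What to change.** - Define the primary set as all randomised patients, analysed as randomised and using every available BMI value.
- Pre-specify one missing-at-random method: either multiple imputation by arm, using all in-between BMI values, before the GEE; or a likelihood-based repeated-measures model. Replacing GEE is an option, not a requirement.
- Apply the same imputation to HbA1c, systolic blood pressure and lipids before the ANCOVA, drawing on their in-between values.
- Keep the set with a follow-up assessment as a sensitivity analysis, and say whether that means any later value or the 2.5-year value.

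The cost is wording and modest programming; the in-between values are already due to be extracted. The downside is reliance on missing at random and on the imputation or covariance model.

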#### Secondary outcome measures

The secondary outcomes will be change between baseline and 2.5 years follow-up of:Clinical measures: systolic blood pressure, HbA1c, lipid profile (total cholesterol, LDL, HDL, triglycerides);Diabetes self-management behaviour (self-care, physical activity, dietary intake, medication adherence);Proactive coping;Quality of Life;Cost-effectiveness of the intervention (total health care resources use during the entire study period).

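### HbA1c, systolic blood pressure and lipids get a two-point ANCOVA although in-between values are extracted; unless imputation uses those values, patients without a 2.5-year value contribute nothing

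*Protocol article*

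**What the plan says.** The section on secondary outcome measures fixes the endpoint at one time point: "The secondary outcomes will be change between baseline and 2.5 years follow-up of" the listed variables, which include systolic blood pressure, HbA1c and the lipid profile.

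Under Clinical measures, these variables and BMI come from one source: "BMI, systolic blood pressure, HbA1c and lipid profiles will collected from the electronic medical record at baseline and 2.5 years follow-up". The next sentence adds: "Clinical measures in-between will also be extracted from the electronic medical record of the GP". No measurement frequency is given for HbA1c, blood pressure or lipids. Three-monthly measurement is stated only for weight, under Sample size.

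Under Statistical analyses, BMI and the other clinical variables part ways. For BMI: "The primary outcome will be analysed by using Generalized Estimated Equations (GEE) for repeated measures". For everything else: "The secondary outcomes will be analysed with ANCOVA on the change from baseline to follow-up". The efficacy analysis is described as "including all patients from whom a follow-up assessment is available", followed by: "If necessary a multiple imputation technique will be used for missing data". That last sentence is not limited to the primary outcome.

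The only figure on attrition is under Sample size: "With an expected drop-out rate of 20%, we need to include a total of 106 patients".

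**The concern.** The same record supplies repeated values of BMI and of the other clinical measures, yet only BMI is modelled over time. A two-point ANCOVA without imputation can use only patients who have the 2.5-year value. Someone whose HbA1c was recorded at, say, one and two years but not at 2.5 years is left out, and the values that best predict the missing one are not used.

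There are two possible costs. One is precision. The other is bias, if patients go missing because of their interim control and do so differently in the two arms. Such a difference is conceivable, because participants are not blinded and only one arm attends the course and booster session. The study's aim includes long-term effects on cardiovascular risk, and blood pressure, HbA1c and lipids carry much of that claim.

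**Working it through.** **The plan's own figure.** The only sample size stated is for BMI: difference 0.77, SD 1.7, six AR(1) measurements with correlation 0.70, alpha 0.05 (taken as two-sided), power 80%.
- Variance of the mean of six such measurements, relative to one: [6 + 2(5×0.7 + 4×0.7² + 3×0.7³ + 2×0.7⁴ + 0.7⁵)]/36 = 20.27/36 = 0.563.
- n per arm = 2(1.960 + 0.842)² × 1.7² × 0.563 / 0.77² = 43.1, so 44. This agrees with the article.

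No figure is given for the secondary outcomes, so the rest rests on assumptions, stated as they arise.

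**How many patients could be affected.** If the 20% BMI allowance also applied to the clinical secondary outcomes, 106 × 0.8 = 84.8 patients (42.4 per arm) would have a 2.5-year value and about 21 would not. The standard error of a completer-only ANCOVA would rise by a factor of 1/√0.8 = 1.12 over no loss.

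**Precision.** The quantity compared is the variance of the same baseline-adjusted contrast at 2.5 years.
- With no missing 2.5-year values, the repeated-measures model and ANCOVA have the same variance (ratio 1.00).
- With 20% drop-out spread evenly over visits, the ratio of repeated-measures to completer-ANCOVA variance is:

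| Assumed correlation | Visits incl. baseline | Ratio |
|---|---|---|
| AR(1) 0.7 | 11 | 0.98 |
| AR(1) 0.7 | 6 | 0.96 |
| Equal 0.5 | 6 | 0.97 |
| Equal 0.7 | 6 | 0.96 |
| AR(1) 0.9 | 6 | 0.93 |

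- With one interim value seen in everyone and a fraction p missing at the end, the ratio is 1 − p·r², where r is the partial correlation of the interim and final values given baseline. If all three correlations are 0.55, r = (0.55 − 0.55²)/(1 − 0.55²) = 0.355, and the cut is 0.2 × 0.126 = 2.5%. If interim-final is 0.80 and the other two are 0.55, r = (0.80 − 0.55²)/(1 − 0.55²) = 0.713, and the cut is 0.2 × 0.509 = 10%.

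The gain is therefore about 2-10%. It is equivalent to moving from 42.4 completers per arm to between 42.4/0.98 = 43 and 42.4/0.90 = 47, against 53 randomised. The difference detectable with 80% power, 2.80 × √(2/n) in residual SDs, is 0.61 with completers, 0.58-0.60 with the interim values and 0.54 with no loss.

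**Bias.** This was checked by simulation with one interim value, correlations of 0.55-0.80, and missingness depending on the interim value in one arm only.
- Log-odds 1 per SD, base rate 20%: completer ANCOVA is biased by 0.05-0.10 SD (0.06-0.12 SD at a 25% base rate).
- Log-odds 0.5 per SD, base rate 20%: about 0.02-0.05 SD.
- Same dependence in both arms: about zero.
- Regression imputation by arm using the interim value, then ANCOVA: below 0.005 SD in every one-arm setting. A likelihood model using the interim value is likewise essentially unbiased.

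For scale, the standard error with 42.4 per arm is √(1 − ρ²) × √(2/42.4), where ρ is the baseline-final correlation: 0.18 SD at ρ = 0.55 and 0.16 SD at ρ = 0.70. A bias of 0.05-0.10 SD is roughly 0.3-0.6 of a standard error.

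**The case against.** The strongest reply is that the method fits the endpoint. The secondary outcomes are defined as change to 2.5 years, and a baseline-adjusted ANCOVA is a standard, valid estimator of that contrast. This stands.

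A reader might infer that the plan definitely discards these patients. The documents do not support that. The imputation sentence is not confined to BMI, and imputation that used the interim values would keep the patients and remove the bias. The trigger and the imputation variables may properly sit in a statistical analysis plan that is not shown. What remains is that this article makes imputation conditional, next to an analysis set limited to patients with a follow-up assessment, and states no use of the interim values.

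A reader might also expect a large loss of efficiency, by analogy with BMI, where six measurements need 44 per arm and a single one would need 77. That gain belongs to an effect averaged over follow-up, which is not the declared secondary endpoint.

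Two further objections stand. The 20% is a BMI drop-out allowance. Because the values come from the GP record, leaving the course or not returning questionnaires need not mean a missing HbA1c or blood pressure. And the document gives no basis for assuming strong missingness in one arm only, so the bias figure is conditional.

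**Conclusion.** The point holds as a minor improvement to a stated method, for HbA1c, systolic blood pressure and lipids only. Under an unimputed ANCOVA, interim values already being extracted would not help, and patients lacking the final value would drop out of the comparison.

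The variance saving is roughly 2-10% if about 20% of final values are missing, and nil if none are. The avoidable bias is about 0.05-0.10 SD, and only under strong dependence of missingness on interim control in one arm. Both ranges rest on assumed correlations and on the borrowed 20%. The primary BMI analysis is not touched, and the questionnaires are not affected because they are measured only at baseline and 2.5 years. The documents do not support calling the ANCOVA invalid.

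**What to change.** For HbA1c, systolic blood pressure and each lipid, keep the 2.5-year contrast as the estimate and choose one of two routes:
- a baseline-adjusted, likelihood-based repeated-measures model with time-by-arm terms, including every patient with any post-baseline value; or
- the planned ANCOVA after multiple imputation that is committed to in advance, done by arm, and includes the in-between values.

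Copying the BMI model is not a substitute, because it is GEE, which is not generally valid when data are missing at random. Keep ANCOVA for the questionnaires.

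The cost is wording and some extra programming. No new data are needed. Time windows for routine-care values will have to be defined, since the article gives neither windows nor a measurement frequency for these variables, and irregular records may make this the larger part of the work.

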### Cost-effectiveness

Lifetime costs and health effects (based on the EQ 5D) will be estimated using a modified probabilistic diabetes model. This validated model has been used before and is described in more detail elsewhere [28–30]. In brief, the model simulates the natural history of type 2 diabetes and calculates costs and quality-adjusted life years (QALYs) for Dutch T2DM patients [30]. The model includes a health state for cardiovascular disease (CVD; myocardial infarction, stroke, peripheral arterial disease), microvascular complications (end-stage renal disease, retinopathy and neuropathy), uncomplicated type 2 diabetes and death. The model computes the occurrence of the above-mentioned diabetes-related complications and the excess mortality due to diabetes. Based on the estimated events and prevalence of complications, it computes diabetes-related lifetime medical costs and QALYs.

To calculate lifetime costs and outcomes, each health state is assigned a value in terms of medical costs and utility (health-related quality of life), and this value is multiplied by the prevalence of the health states over time.

In addition to the model input data described above, medication costs of glucose-lowering drugs, anti-hypertensive medication and cholesterol-lowering drugs used during the total follow-up period will be included in the cost calculation. Costs of the BGI-course and total health care resources (including consultations of the dietician) use during the whole study period will also be included in the cost calculation. These costs will be extrapolated to estimate lifetime medication costs, assuming that the cost difference between the BGI-group and the control-group remains constant over time.

The model will calculate two lifetime health outcomes (life years, QALYs) and costs for each patients (discounted and undiscounted). To correct for confounding and improve model estimates of the difference in outcome between the BGI-group and the control-group, the following baseline covariates will be used: age, sex, duration of diabetes, history of cardiovascular disease, smoking, HbA1c, systolic blood pressure, total cholesterol and HDL cholesterol.

The primary outcome of the cost-effectiveness analyses will be the cost-effectiveness of BGI versus control, expressed as the incremental cost-effectiveness ratio (ICER), calculated by dividing the incremental costs by the incremental QALYs or incremental life years. Uncertainty surrounding the cost-effectiveness ratios as calculated from the model will be expressed using a cost-effectiveness plane. A cost-effectiveness acceptability curve will be created to determine whether implementation of BGI is cost-effective given different thresholds of willingness to pay for a QALY (e.g. a threshold of € 20.000 per QALY).

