**Methods:**

Randomised controlled trial with 2.5 year follow-up. Adults (≤75 years) with a type 2 diabetes duration between 3 months and 5 years will be included. With the use of a self-management screening tool (SeMaS) their potential barriers of self-management due to depression and/or anxiety will be determined. Based on the results of the SeMaS selection patients will be randomised (1:1) to the BGI-group (n = 53) or the control-group (n = 53). In addition to receiving usual care, patients in the BGI-group will follow the 12-week theory-based self-management program and a booster session a few months thereafter. The control-group will receive care as usual. The primary outcome is change in Body Mass Index after 2.5 years follow-up. Secondary outcomes are HbA1c, lipid profile and systolic blood pressure, (diabetes) quality of life, level of physical activity, dietary intake and medication adherence and proactive coping. Cost-effectiveness will be based on total use of health care resources during the entire study period. Difference between groups in change over time will be analysed according to intention-to-treat analysis.

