## Background

Diabetes self-management forms a major part of diabetes treatment and involves several complex behaviours, such as adhering to a treatment regimen, monitoring symptoms, maintaining a healthy lifestyle and managing the impact of the disease on one’s life. People with type 2 diabetes mellitus (T2DM) are expected to take more and more responsibility in this, but for many of them self-management is difficult to incorporate in daily life and not all patients will possess the necessary skills for this. The motivation to initiate changes in behaviour is often present, but patients do not know what needs to change or maintain the achieved behavioural lifestyle when barriers are encountered. We developed the Beyond Good Intentions (BGI) program to enhance the ability of patients to act upon their intentions. It is based on the theories of self-regulation and proactive coping [1], assuming that people should control and direct their actions in order to meet their goals. Pro-active coping refers to efforts undertaken in advance of a potentially stressful event to prevent or modify its form before it occurs [1]. BGI has proven to be effective in patients with screen-detected T2DM up until 9 months follow-up [2]. Based on a computer-based simulation model to project long-term health benefits and cost-effectiveness, BGI was among the four diabetes self-management programs worldwide, with a minimum follow-up of 12 months, with the best cost-effectiveness ratio [3]. However, real, not modelled, long-term data on (cost-) effectiveness of BGI are lacking and also its effectiveness in people who are known with T2DM and not screen-detected, is unclear.

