Group based educational programs for diabetes self-management can improve blood glucose, blood pressure, body mass index (BMI) and the requirement of blood glucose lowering drugs; however, the long-term results were varying [4]. In Italy, non-insulin-treated T2DM patients known with diabetes for at least 1 year were randomised to either group or individual care in a hospital-based setting. After 4 years clinical, cognitive, and psychological outcomes were better in the group based treatment [5]. In the DESMOND trial, greater improvements in weight loss and smoking cessation were found in the intervention group at 1-year-follow-up, but at 3-year-follow-up this effect was no longer apparent [6, 7]. In general, completers of a diabetes self-management intervention study are significantly more highly educated than dropouts [8]. This indicates that interventions to improve self-management should be tailored to different categories of patients. The ‘one size fits all’ principle in diabetes education research is outdated. To estimate a priori the chance of successful self-management of a patient, the self-management screening tool (SeMaS) can be used [9]. With SeMaS possible barriers for self-management due to depression and/or anxiety can be detected. Both depression and anxiety can interfere with the effectiveness of a self-management program at that moment for a particular person and should be dealt with before following the program. Besides, individuals with already high self-management capabilities are likely to have no additional benefit from an educational course [10–12].

We hypothesise that by differentiating between patients who may and those who may not benefit from a self-management program, a more (cost-) effective self-management education program can be designed which is also effective on the long-run. Therefore, the aim of the current study is to investigate the cost-effectiveness and long-term effects of the educational program BGI on cardiovascular risk, quality of life and diabetes self-management behaviour in a preselected group of known T2DM patients.

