#### Cost-effectiveness

Data on health care resources use during the whole study period will be extracted from electronic medical records from the general practitioners and for health status the EQ 5D questionnaire will be used at baseline and after 2.5 years follow-up.

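### The trial is justified by a lack of observed long-term cost-effectiveness data, but the only cost-effectiveness result described is a lifetime ICER from a simulation model

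*Protocol article*

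**What the plan says.** **Rationale.** The Background reports that BGI already ranked well among self-management programmes in an economic comparison that was itself a projection: "Based on a computer-based simulation model to project long-term health benefits and cost-effectiveness". It then names what is missing: "real, not modelled, long-term data on (cost-) effectiveness of BGI are lacking". The section closes by putting economics in the objective: "the aim of the current study is to investigate the cost-effectiveness and long-term effects of the educational program BGI".

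**Promise.** The Abstract (Methods) says "Cost-effectiveness will be based on total use of health care resources during the entire study period", and the cost-effectiveness item under Secondary outcome measures says much the same. The Discussion counts cost-effectiveness at 2.5 years among the study's contributions.

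**Data.** Under Measurements, the Cost-effectiveness paragraph takes resource use over the whole study from general practice records, and "for health status the EQ 5D questionnaire will be used at baseline and after 2.5 years follow-up".

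**Analysis.** The Cost-effectiveness section that follows Statistical analyses begins: "Lifetime costs and health effects (based on the EQ 5D) will be estimated using a modified probabilistic diabetes model". Health states are given a cost and a utility, and these are multiplied by how common each state is over time. Medication, course and resource-use costs from the trial enter the calculation and are projected beyond follow-up with an unchanging difference between arms. The main economic result is an ICER, and "Uncertainty surrounding the cost-effectiveness ratios as calculated from the model will be expressed using a cost-effectiveness plane".

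**The concern.** The Background sets modelled evidence, which exists, against observed evidence, which does not. A trial that then reports only a modelled lifetime ratio adds another estimate of the kind already available, although with better inputs.

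What is at stake is how readable the economic result will be. A lifetime ICER combines what happened in the trial with simulated complications, assigned utilities and a cost difference assumed to persist for life. Without a result confined to the observed period, a reader cannot tell how much of the ratio the trial showed and how much the model supplied. The 2.5-year figure announced in the Discussion would not be available.

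**Working it through.** The document gives no figure to reproduce here. The check sets the stated question beside each planned analysis and asks whether any of them yields a result for the observed period.

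1. **Question.** Background: observed, as opposed to modelled, long-term cost-effectiveness. Discussion: cost-effectiveness at 2.5 years. Together these call for incremental costs and incremental QALYs over the 2.5 years of follow-up.

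2. **Does the economic analysis section provide that?** Its horizon is lifetime. Its outputs are lifetime life years, lifetime QALYs and costs. Its ratios are described as coming from the model, and the plane displays the uncertainty in those ratios. No result with a 2.5-year horizon is mentioned.

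3. **Does the use of trial costs in the model provide it?** Observed costs are an input. The section extends them past follow-up under a constant difference between arms, so the reported cost difference is not the observed one.

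4. **Does the phrase about effects being based on the EQ-5D provide it?** The same section explains that utilities are attached to health states and weighted by their prevalence over time. That is a modelled QALY, not one built from each patient's two questionnaires.

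5. **Does the Statistical analyses section provide it?** Secondary outcomes get ANCOVA on change from baseline, and quality of life, including EQ-5D, is a secondary outcome. This can give a difference in utility at 2.5 years. It gives no incremental cost and no ICER, and no step from utility to QALYs is described.

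6. **Could the collected data provide it?** Yes. Resource use covers the whole study, and utility is measured at both ends. With utilities u0 at baseline and u1 at 2.5 years, and linear change assumed between them, the undiscounted QALYs per patient are 2.5 × (u0 + u1) / 2 = 1.25 × (u0 + u1). Incremental QALYs then come from a regression of this quantity on arm and u0.

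Steps 2 to 5 find no observed-period result. Step 6 shows that one can be obtained from data already planned.

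**The case against.** The strongest reply has four parts.

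- **The gap named in the Background covers effectiveness as well as cost-effectiveness.** Effectiveness is answered: BMI and the secondary outcomes are analysed on observed data. This stands. A reader might infer that the trial leaves its whole question unanswered, and the document does not support that. Only the cost-effectiveness half is affected.

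- **Trial data drive the model.** A fair reading is that inputs observed over 2.5 years replace the shorter-term inputs of the earlier projection. This stands as a description of the model's merit, but the result is still modelled.

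- **The Abstract and the secondary outcome list need not promise a 2.5-year ratio.** They can be read as naming the source of the cost data, which the model does use. This also stands. The mismatch rests on the Background and the Discussion.

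- **A journal article condenses, and a fuller document may hold a within-trial analysis.** The article does speak of cost-effectiveness analyses in the plural. But it states the horizon, the method, the main economic outcome, the covariates and the display of uncertainty. The conflict is between things it says, not a detail that it leaves out.

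**Conclusion.** The point holds as an inconsistency between the stated rationale and the stated economic analysis. The article says observed long-term cost-effectiveness is missing and announces a 2.5-year answer, yet the only cost-effectiveness result it describes is a modelled lifetime ICER. The conclusion rests on the article's own text and on no assumed number. It touches a stated aim and a secondary outcome, and leaves the BMI analysis untouched. It is worth correcting, but it does not threaten the trial's main conclusion.

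Two stronger readings are not supported.

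- **Baseline utility.** Baseline EQ-5D is not among the listed adjustment covariates, so a reader might infer that a chance imbalance in baseline utility passes directly into the planned QALY difference, and might put a euro value on it. The planned QALYs come from utilities assigned to health states, and nothing says that a patient's own baseline utility is carried forward. Such a value would describe an unadjusted within-trial calculation that is not planned. Multiplying the imbalance by the full 2.5 years would also assume that it persists undiminished.

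- **Primacy.** A reader might infer that the within-trial analysis must replace the lifetime model as the main economic analysis. The inconsistency does not require that. A lifetime model is a legitimate way to reach a lifetime horizon, and the order of the two is a matter of choice.

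**What to change.** Alongside the lifetime model, add a within-trial cost-utility analysis over 2.5 years:

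- **Costs:** those observed per patient during the study, including the course.
- **QALYs:** area under the curve from the EQ-5D utilities at baseline and 2.5 years.
- **Adjustment:** regression of QALYs with baseline EQ-5D utility as a covariate. It is needed here because baseline utility enters this QALY directly.
- **Uncertainty:** bootstrap of patients, keeping costs and QALYs paired, shown on a plane and an acceptability curve.
- **Reporting:** incremental costs, incremental QALYs and the ICER for the observed period, with the lifetime result labelled as extrapolation.

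The cost is some extra analysis, with no new visits, questionnaires or patients. The drawback is that only two utility points span 2.5 years, so linear change between them must be assumed and reported as a limit. A temporary effect soon after the course would be missed.

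If this analysis is not added, the Background and Discussion should at least say that cost-effectiveness will be modelled, and the Abstract and the secondary outcome should be worded to match. That removes the contradiction but leaves the stated gap open.
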